**Fig. 1 Fig1:**
[figure not shown]
Anticipated recruitment, randomisation and assessment of participants

**Table 1 Tab1:** SPIRIT flow diagram: schedule of enrolment, interventions, and assessments

	Study Period							
	Enrolment	Allocation	Post-allocation					Close-out
TIMEPOINT	-t_1_	0	t_1_ baseline	t_2_ 5 weeks	t_3_ 6 months	t_4_ 12 months	t_5_ 24 months	t_6_ 36 months
**ENROLMENT**								
Eligibility Screen	X							
School enrolment	X							
Allocation		X						
Informed consent			X					
**INTERVENTION**								
Health education as usual (active control)								
OurFutures Vaping program (intervention)								
**ASSESSMENT**								
Primary Outcomes			X	X	X	X	X	X
Secondary Outcomes (except RUQ & SDQ)			X	X	X	X	X	X
Secondary Outcomes (RUQ & SDQ)			X	X		X	X	X
Process outcomes				X				

*Note: RUQ = Resource Use Questionnaire; SDQ = Strengths & Difficulties Questionnaire.*

#### Informed consent

Participant information statements and consent forms will be distributed to parents/guardians via hardcopy or electronically (depending on school preference). Due to differing requirements across ethics committees, some schools will use passive (opt-out) parental consent, while others will use active (opt-in) parental consent. If insufficient active written parental consent is obtained from a school, verbal parental consent will be sought from the remaining parents. A school staff member will contact parents using contact details available to the school and will either be reimbursed for their time and effort, or the school will be reimbursed the costs of employing a casual teacher for a day. Students will be required to provide active written consent prior to the baseline assessment. Active written consent will also be sought from Year 7/8 teachers at both control and intervention schools to complete online evaluations and fidelity logbooks.

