#### Randomisation

The *blockrand* package in R [37] will be used to generate an unpredictable, concealed random allocation sequence. After schools’ consent and enrolment in the study, a biostatistician with no role in school recruitment will use the package to block randomise schools to study groups, with stratification by state and school gender mix (coeducational, predominately male [> 60%], or predominately female [> 60%]). Automatic randomisation removes any researcher involvement, and the allocation will be concealed from the investigators and all research personnel (blinded), except those with direct school involvement where blinding is not possible (e.g., Research Assistants who will need to discuss intervention delivery with teachers). Twenty-one schools will be randomly allocated to the *OurFutures Vaping Program* intervention group and 21 schools to an active control group. Figure 1 provides an overview of the anticipated recruitment and randomisation process, and Table 1 presents the SPIRIT flow diagram schedule of enrolment, interventions, and assessments.

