### Analysis

#### Intervention effects

Data analysis will be conducted on an intention-to-treat basis, whereby all randomised students will be analysed in the groups that they were originally assigned. Generalized mixed effects regression will investigate whether receiving the intervention reduces the likelihood of primary and secondary outcomes (e.g., logistic regression for dichotomous outcomes, poisson regression for count outcomes, linear regression for continuous outcomes). Analyses will be conducted in R, using the *lme4* package [65]. To account for within-person and within-school dependency in the data, models will include participant and school as nested random intercepts; and participant and time as random slopes. We will also test different specifications of time (linear, quadradic & categorical) to determine the best fitting model for the data. Model fit will be compared using likelihood ratio tests, AIC and BIC statistics. The effect of greatest interest will be the time × group interaction for the primary outcome, which reflects the relative average 12-month change in the log odds of the outcome for the intervention group compared to control, adjusting for baseline differences. Due to loss to follow-up, we reasonably expect some outcome data to be missing. Mixed-effects models use maximum likelihood estimation (MLE), producing unbiased estimates when data is assumed to be not missing completely at random. Missing data will be explored by examining baseline differences on the outcome and other potential confounding variables between those retained and those lost to follow-up. Sensitivity analysis will examine the impact of potential covariates related to missingness by including those predictors in the imputation model during multiple imputation.

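### Allocation precedes the only scheduled informed consent and the baseline survey, and nothing keeps the arm from schools until both are complete

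*Protocol article*

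**What the plan says.** On the order of events, the Randomisation section of the protocol article states: "After schools’ consent and enrolment in the study, a biostatistician with no role in school recruitment will use the package to block randomise schools". Table 1 marks allocation at timepoint 0. It marks "Informed consent" once, at t1 baseline, which is the first column under "Post-allocation". The first measurement of the primary outcome is in the same t1 column.

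On student consent, the Informed consent section states: "Students will be required to provide active written consent prior to the baseline assessment". On parents, it explains that requirements differ between ethics committees, so that "some schools will use passive (opt-out) parental consent, while others will use active (opt-in) parental consent". For the opt-in schools it adds: "If insufficient active written parental consent is obtained from a school, verbal parental consent will be sought from the remaining parents". That follow-up is made by a member of the school's staff, for which the staff member or the school is reimbursed. No threshold for insufficient consent is given.

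On who knows the arm, the Randomisation section conceals allocation from investigators and research personnel, "except those with direct school involvement where blinding is not possible". Its example is research assistants who talk to teachers about delivering the program.

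On the analysis set, the Intervention effects section states that "all randomised students will be analysed in the groups that they were originally assigned".

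**The concern.** In a cluster trial, concealing the sequence protects the allocation of schools. It does not protect the entry of students if they are recruited after their school's arm is known. A family, a student or a staff member seeking consent may act differently when the vaping program is known to be coming than when lessons will continue as usual. The two arms can then contain different kinds of students before any lesson is taught.

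Intention-to-treat does not correct this. It keeps students in the arm of their school, but the imbalance arises earlier, when students come into the data. What is at stake is the comparison of 12-month uptake, because a student's underlying risk of starting to vape may influence both consent and outcome.

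**Working it through.** The article gives no figure to reproduce here. The check has two parts: the sequence of events, and an illustration of scale.

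**Sequence**

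1. Randomisation follows the school's own consent and enrolment (Randomisation section). It is not made conditional on student consent, parental consent or baseline.
2. In Table 1, allocation is at 0, and informed consent and the first outcome survey are at t1. Student consent must come before the baseline survey (Informed consent section), and the table places both after allocation.
3. Staff who work with schools are unblinded, and intervention schools must learn their arm in order to deliver the program. No passage says that this happens only after consent and baseline, or that the people seeking consent are masked.
4. Table 1 has one undivided consent row, and the text does not date parental consent. Its position relative to allocation is therefore open.

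So students enter after allocation, and entry with the arm known is permitted though not stated.

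**Scale (assumed inputs, no true effect, crude 12-month comparison)**

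Assumptions, none of them from the article: 10% of students are high-risk with 60% uptake; overall uptake is 20%; consent is 80% for everyone except high-risk students in intervention schools. The design odds ratio of 0.7 is from Sample size calculations.

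- Low-risk uptake: (0.20 − 0.10 × 0.60) / 0.90 = 0.1556.
- Control arm: uptake 0.20, odds 0.25.
- High-risk consent of 60% in the intervention arm (a 20-point gap): (0.72 × 0.1556 + 0.06 × 0.60) / 0.78 = 0.148 / 0.78 = 0.190. Odds 0.148 / 0.632 = 0.234; odds ratio 0.234 / 0.25 = 0.94.
- High-risk consent of 40% (a 40-point gap): (0.112 + 0.024) / 0.76 = 0.136 / 0.76 = 0.179. Odds 0.136 / 0.624 = 0.218; odds ratio 0.218 / 0.25 = 0.87.

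On the log scale, as a share of ln 0.7 = −0.357, these are about 0.065 / 0.357 = 18% and 0.137 / 0.357 = 38% of the design effect. If the gap ran the other way, the odds ratios would be 1 / 0.937 = 1.07 and 1 / 0.872 = 1.15, which would hide a benefit.

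A second set of assumptions lets consent depend on ever-use itself. Prevalence then cancels, and the spurious odds ratio is the ratio of consent rates of users to non-users in the intervention arm, when these rates are equal in the control arm: 0.85 / 0.90 = 0.94, 0.80 / 0.90 = 0.89 and 0.60 / 0.80 = 0.75. Only a large gap comes near 0.7. So far as the selection is on vaping already present at baseline, the planned baseline adjustment would absorb part of it.

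In the first illustration, overall consent is 80% in control against 78% or 76% in intervention schools. A small difference in total consent can thus accompany a large gap in one subgroup, so consent rates alone would not settle the matter.

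**The case against.** The strongest reply is that allocation at time 0 is not disclosure at time 0. The article does not say when schools learn their arm, and a condensed article may leave that step to the full protocol. This stands as a limit on the claim: knowledge of the arm at consent is something the text permits, not something it reports. But the order in Table 1 is stated, and nothing in the article offsets it.

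Three stronger readings are tempting, and the article supports none of them:

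- A reader might infer that parental consent always follows allocation. It is not dated separately, and forms could go out earlier.
- A reader might infer that school staff pursue consent everywhere. The follow-up applies only to opt-in schools with insufficient written consent. The rule is the same in both arms, and by raising coverage it may even reduce selection.
- A reader might infer that baseline vaping answers define who is at risk of uptake, so that answers given with the arm known would distort the analysis set. No at-risk set or exclusion of baseline ever-users is stated; the analysis uses change from baseline in all students.

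The article also contains mitigations. Sample size calculations expects nearly all students to take part, which would leave little room for selection; that is an expectation, and the consent section itself plans for shortfalls. The effect of interest is a time × group interaction adjusted for baseline differences, which deals at least partly with imbalance in existing vaping. It does not deal with unmeasured risk of later uptake among students who have not yet vaped.

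Finally, the phrase about randomised students can be read loosely as students of randomised schools. That is a fair reading, but the students analysed are those who consented after their school was allocated, and a precise definition is easy to give.

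**Conclusion.** The point holds as a design risk. The stated sequence puts student entry after allocation, school-facing staff are unblinded, and no safeguard keeps the arm from schools until consent and baseline are complete. Differential recruitment by arm is therefore possible, and neither intention-to-treat nor baseline adjustment removes the part that acts through unmeasured risk of later uptake.

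The article gives no evidence that such an imbalance occurred or would favour the intervention. The crude odds ratios of about 0.94 and 0.87 rest on assumed one-directional gaps of 20 and 40 points confined to a high-risk tenth of students. They are not estimates of bias in the planned adjusted interaction. Small gaps would give modest bias. The case for change is that a recognised source of bias can be closed at low cost.

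**What to change.** Do not disclose allocation to a school, or to anyone seeking consent there, until that school's consent list is closed and its baseline survey is done. If timetabling within Term 2 prevents this, have consent sought by people masked to arm. State in the protocol when schools learn their allocation and when parental consent is obtained relative to it.

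In either case, report consent rates by arm with the enrolled cohort as denominator, together with baseline characteristics by arm. Define the analysis set as all consented students of randomised schools, analysed by their school's allocation, in place of the wording on randomised students. The reporting and the definition remain possible even if recruitment has begun.

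The cost is shorter notice for intervention schools. Table 3 places baseline, the program and the post-intervention survey all in Term 2, and Table 1 puts that survey at five weeks, so the constraint is real. It is softened because, as the introduction says, the lessons directly replace regular health lessons. Reporting consent by arm costs almost nothing.

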#### The OurFutures Vaping Program

Schools allocated to the intervention group will implement the *OurFutures Vaping Program* in health education classes in 2023. The program involves four 40-minute lessons, ideally delivered one week apart. Each lesson consists of a web-based cartoon component (see Fig. 2) completed individually by students (approx. 20 min), followed by optional teacher-facilitated activities (e.g., quizzes, class discussions, role plays). There are quizzes and reflective activities embedded in the cartoons to ensure student engagement, comprehension, and critical thinking. Factsheets are provided after each lesson to summarise and reinforce key content.

**Fig. 2 Fig2:**
[figure not shown]
Example cartoon from the *OurFutures Vaping Program*

In line with the *OurFutures* prevention model and principles of effective tobacco and e-cigarette prevention programs [19, 20, 27], the *OurFutures Vaping Program* adopts a harm minimisation and comprehensive social influence approach [38]. This includes providing evidence-based information about e-cigarettes and tobacco smoking, normative education to correct misperceptions on use, and resistance skills training. Whilst focused on e-cigarettes, the program takes an integrated approach in addressing e-cigarette use and tobacco cigarette use. Although they are distinct behaviours with unique characteristics, simultaneously targeting both behaviours by addressing core principles that have been effective in tobacco and drug prevention is an efficient and cost-effective strategy. An overview of the *OurFutures Vaping Program* content is provided in Table 2.

**Table 2 Tab2:** Overview of the *OurFutures Vaping Program* content

Lesson	Key messages
**1**	• The harmful chemicals in e-cigarettes • Prevalence and patterns of vaping/cigarette smoking • Short- and long-term consequences of vaping • Reasons young people choose to, or not to, vape
**2**	• The positive portrayal of vaping on social media • Vaping and smoking as ineffective ways to cope • Nicotine and the developing brain • Where to seek help for vaping, smoking and mental health • Assertive communication and refusal skills
**3**	• Vaping/smoking and the law • Short- and long-term consequences of smoking cigarettes • Marketing tactics and the influence of social media • The links between vaping and smoking • Help-seeking for vaping, smoking and mental health
**4**	• Assertive communication and refusal skills • Signs of nicotine dependence • Where to seek help and strategies to break the cycle of nicotine dependence • The benefits of avoiding or stopping vaping

Consultations were conducted with students and teachers throughout the design phase to construct character profiles and storylines for the cartoons and ensure the program was feasible, acceptable, and well aligned with the latest evidence and health education curricula. This included student surveys, focus groups, interviews, and input from end-users through several public webinars, school presentations and Q&A sessions. Finally, the materials underwent expert review to ensure it aligned with the latest scientific evidence. Modifications were made based on the feedback provided by these groups. This process builds on the extensive development work conducted for the previous *OurFutures* programs, which were co-designed and refined by > 210 young people and > 390 teachers, parents, and health and education experts.

#### Active control condition

Schools allocated to the control condition will implement health education as usual in their Health and Physical Education lessons. As drug education is mandatory within the Australian health education curriculum, these schools serve as an ‘active control’. A logbook will be completed by teachers at control schools to understand the amount and format of e-cigarette or tobacco cigarette education delivered to their Year 7/8 students. Control schools will be offered access to the intervention at the end of the study.

#### Assessments

All students in control and intervention groups will be invited to complete an online self-report survey in a supervised classroom setting at baseline, immediately post intervention, and 6-, 12-, 24- and 36-months post baseline to examine lasting effects (see Table 3). Students absent for follow-up surveys will be contacted by research staff (using details provided during registration) and invited to complete the survey outside of school time. Hardcopy surveys will be made available to schools/participants on request, with data entered and checked by project personnel. All data will be deidentified and linked using a unique code assigned at baseline. Upon completion, students will go into a random draw to win a $100 gift voucher, with two vouchers available per school on each assessment occasion. These strategies have been successful in previous school-based trials run by the research team, resulting in outstanding retention rates, even during the COVID-19 pandemic when there were significant disruptions to schooling (85% at 12 months and 75% at 24 months) [39].

**Table 3 Tab3:** **Intervention and assessment timeline**
*(F/U = follow up)*

	Baseline	OurFutures Vaping Program	Post-intervention follow-up	6-mth follow-up	12-mth follow-up	24-mth follow-up	36-mth follow-up
**Year**	2023	2023	2023	2023	2024	2025	2025
**Time**	Term 2	Term 2	Term 2	Term 4	Term 2	Term 2	Term 2
**Age**	12–14	12–14	12–14	12–14	13–15	14–16	15–17
**Intervention Group**	✓	✓	✓	✓	✓	✓	✓
**Control Group**	✓	-	✓	✓	✓	✓	✓

### Measures

#### Primary outcome

The primary outcome is change over time in self-reported e-cigarette use among the intervention group, over and above change in the control group. Specifically, uptake of e-cigarette use. To assess this, students will be asked “Have you ever used a vape, even one or two puffs?” (Yes/No). The primary endpoint will be the 12-month follow-up.

#### Secondary outcomes

*Tobacco ever use.* Assessed using a single item: “Have you ever tried smoking a cigarette, even one or two puffs?” (Yes/No). This item was based on items used in our previous trials [39] and the Standard High School Youth Risk Behaviour Survey [40].

*Frequency and quantity of e-cigarette and tobacco cigarette use.* Assessed using a series of questions based on those used in previous research [36, 39, 41] and the National Drug Strategy Household Survey [42].

*Knowledge about e-cigarettes and tobacco cigarettes.* Measured using a 15-item scale developed to reflect the content of the *OurFutures Vaping Program* intervention. The scale was derived from a larger pool of items that was piloted among adolescents to reflect items of varying degrees of difficulty. The items assess a range of topics such as the short- and long-term effects/harms of e-cigarettes and tobacco cigarettes, common myths about e-cigarettes and tobacco cigarettes, e-cigarette and tobacco cigarette laws in Australia, and the prevalence of e-cigarette and tobacco cigarette use among young people in Australia. Response options include: True/False/Don’t know.

*Motives to use e-cigarettes.* Assessed using an adapted version of the Tobacco Motives Inventory [43]. The scale comprises 15 potential motives for vaping across four subscales: Social Motives, Self-enhancement Motives, Boredom Relief Motives, and Affect Regulation Motives. Items will be rated on a 5-point Likert scale from 0 (not at all true) to 4 (very true).

*Attitudes towards e-cigarettes.* Assessed using an adapted and validated version [44] of the Smoking Expectancy Scale for Adolescents [45]. The scale includes 43 items relating to the potential consequences of smoking an e-cigarette (e.g., “feel more relaxed”, “get hooked”) across eight subscales: Health Costs, Appearance – Presentation Costs, Social Costs, Addiction, Social Benefits, Affect Control, Boredom Reduction, and Weight Control. Items are rated on a 10-point Likert scale from 0 (completely unlikely) to 9 (completely likely).

*Intentions.* Two single items based on those from our previous school-based trials [36, 39] will be used to assess intentions to use e-cigarettes and tobacco cigarettes in the next year. Responses will be rated on a 5-point scale from 0 (Certain not to try) to 4 (Certain to try).

*E-cigarette refusal skill techniques.* Assessed using items adapted from a measure developed to assess drug refusal skill techniques [46]. Participants will report their level of confidence using five refusal skills in a scenario where someone has asked them to vape. Responses will be rated on a 5-point scale from 1 (Very unconfident) to 5 (Very confident).

*Self-efficacy to resist peer pressure.* Assessed using an adapted version of the Resistive Self-Regulatory Efficacy Scale [47], with two items (those relating to the ‘use of crack’ and ‘sexual intercourse’) removed, and an item relating to vaping added. Participants rate each of the 9 items on a 7-point scale from 1 (Not well at all) to 7 (Very well). Items will be summed to generate a total score, with higher scores indicating greater self-efficacy to resist peer pressure.

*Mental health.* Depressive symptoms over the past 7-days will be assessed via the Patient Health Questionnaire-8 (PHQ-8), and 8-item scale validated for use among adolescents [48, 49]. Anxiety symptoms over the past 7-days will be assessed via the Patient Reported Outcomes Measurement Information System [50] using the 13-item anxiety scale from the pediatric item bank. The 6-item Kessler Psychological Distress Scale (K6) [51] will be used to assess symptoms of psychological distress risk for serious mental illness. The K6 has demonstrated good internal consistency in youth samples (α = 0.86) [52]. Internalising and externalising symptoms will be assessed using the 25-item Strengths and Difficulties Questionnaire [53]. Internalising symptoms are determined by summing the Emotional and Peer Problems subscales. Externalising symptoms are determined by summing the Conduct and Hyperactivity subscales. The Short Warwick–Edinburgh Mental Well-being Scale [54] will be used to assess mental wellbeing. The scale comprises 7 items and has been validated among adolescents [55]. Perceptions of Stress which will be measured by the Perceived Stress Scale (PSS), a 10-item self-report scale validated for use with adolescents [56–58].

*Health-related quality of life.* Assessed using the Child Health Utility 9D instrument (CHU9D) [59]. This instrument has been validated for self-completion by young people aged 7–17 years in Australia and can be used to derive utility weights that are, in turn, used to estimate quality-adjusted life years (QALYs) [59].

*Resource utilisation.* The utilisation of healthcare and other related services will be measured using a self-report resource use questionnaire (RUQ) that has been developed for use in previous studies [60, 61]. Participants will be asked to provide self-report data on healthcare resource use, such as: the number of contacts with primary care and specialist healthcare professionals; use of prescription medications; hospital admissions; emergency department presentations; and engagement with headspace services. Additional questions will be asked in relation to educational impacts, including school absence days. Healthcare resource use will be valued using unit prices obtained from publicly available cost schedules, such as the Medicare Benefits Schedule (MBS), Pharmaceutical Benefits Schedule (PBS) and National Hospital Cost Data Collection (NHCDC). Hourly wages will also be based on data provided by schools, where applicable, or the Australian Bureau of Statistics.

